### Secondary outcomes

**Social support**. The Social Provision Scale [SPS-5; 68] will be used to measure social support. The scale consists of 5-items (e.g., “I have relationships where my competence and skill are recognized”; “I feel part of a group who share my attitudes and beliefs”), on a 4-point Likert scale ranging from 1 (*strongly disagree*) to 4 (*strongly agree)*. A total summed score ranging from 5–20 will be used in main analyses, where higher scores indicate more favorable perceptions of social support. The scales validation has been shown in the general population and the post-secondary student population [68].

**Social connectedness.** The 8-item Social Connectedness Scale will be used to measure social connectedness [69]. The items portray a general emotional distance between the self and others (e.g., “I feel disconnected from the world around me”; “I don’t feel I participate with anyone or any group”) and reflect behavior, feelings, or both associated with a lack of connectedness on a 6-point Likert scale ranging from 1 (*agree*) to 6 (*disagree*). Higher scores will reflect a more reported sense of social connectedness with a potential range of 8–48. The Social Connectedness Scale displays strong psychometric properties among post-secondary students [69].

**PA behavior.** Self-reported PA behavior will be measured using the GLTEQ [70]. Students will be asked to indicate how many times on average they engaged in mild (e.g., yoga, golf), moderate (e.g., fast walking, baseball), and vigorous (e.g., running, soccer) PA for more than 15 minutes in a typical week. A common modification of assessing the average duration (in hours and minutes) per session of each intensity category of PA will be included [71–73]. Students will also be asked to report the frequency and average duration of resistance exercise (e.g., free weight, bodyweight training). Total scores for mild, moderate, and vigorous activity and resistance exercise will be calculated by multiplying self-reported times per week by average duration of sessions for each type. The scale has been used among post-secondary students [73] and has been validated for use in adult samples [70,73].

### Implementation process evaluation outcomes

Informed by previous research [14,29], the mixed methods implementation evaluation plan (see Table 3) will assess intervention fidelity, acceptability, reach, and adherence. Intervention fidelity will assess the extent to which students perceive their coach adhered to core intervention targets guided by the COM-B model, as well as the extent to which the collaborative coach–student relationship supported task, goal, and bond components of working therapeutic alliance [74]. Program acceptability will be assessed based on students’ enjoyment, and their perceptions of the program’s effectiveness as a mental health intervention. In addition, motives for engagement, perceptions of the intervention content (i.e., what worked well and opportunities for improvement), and delivery format preferences (i.e., no preference, 1:1, or group-based) will be assessed to help inform future program refinement to improve acceptability. Reach will assess referral pathways, as well as program inclusion and exclusion considerations. Adherence will be assessed based on the number of students who initiated the intervention, the number of sessions completed, and overall student completion rates.

**Table 3 pone.0330851.t003:** Mixed methods implementation evaluation.

Implementation evaluation construct	Method, source of data, example items	
	**Quantitative data**	**Qualitative data**
**Intervention fidelity**		
COM-B core intervention components	Student perceptions of the integration of core COM-B targets by the PA coach across 13-items on a 7-point Likert scale ranging from 1 (*strongly disagree*) to 7 (*strongly agree*) will be used to assess intervention fidelity (see Table 1 for items).	N/A
Collaborative coach-student relationship	The 12-item Working Alliance Inventory will be used [WAI-12; 74]. Aligning with previous research [72], the WAI-12 will be adapted to the PA context (e.g., “My PA coach and I agree on what is more important for me to work on”) and students will be asked to report working alliance perceptions on a 7-point Likert scale ranging from 1 (*never*) to 7 (*always*).	N/A
**Acceptability**		
Enjoyment	3-items (e.g., “I enjoyed the exercise sessions very much”; “The exercise sessions were fun to do”) will be used on a 5-point Likert scale ranging from 1 (*strongly disagree*) to 5 (*strongly agree*).	N/A
Acceptability of the program as a mental health intervention	4-items (e.g., “The program is a useful component of on-campus mental health promotion”; “The sessions were good for my mood and general well-being”) will be used on a 5-point Likert scale ranging from 1 (*strongly disagree*) to 5 (*strongly agree*).	N/A
What worked well and opportunities for improvement		An open-ended survey question asking, “Please describe three likes and three dislikes from the program” will be used to assess general likes and dislikes towards the PA intervention.
Engagement motives and preferences for PA delivery	A closed-ended survey question asking, “Did you have a preference for intervention delivery?” will be used to assess preferences across response options of no preference, one-on-one delivery, and group-based delivery.	If students report a preference for intervention delivery, an open-ended survey question will ask students to describe reasons for their preference. An open-ended survey question asking, “Please briefly describe your reasons for wanting to participate in the intervention” will be used to assess engagement motives.
**Reach**		
	Percentage (%) of students eligible, % excluded, exclusion reasons, and student referral pathways including response options of on-campus health and well-being services, student accessibility services, social media advertisement, and other.	N/A
**Adherence**		
	Number of students who initiated the program, sessions completed, and completion rates.	Reasons for not initiating or completing the program will be recorded.

*Note*. PA = physical activity.

### Sample size

A simulation-based power analysis using the *simr* package in R was conducted [75]. This analysis estimated the likelihood of detecting a group-by-time interaction in a linear mixed model using restricted maximum likelihood. The simulated design included three groups (1:1 PA intervention, group PA intervention, and waitlist control), with primary and secondary outcomes assessed at three time points: pre-intervention (T1), post-intervention (T2), and follow-up (T3). The model included fixed effects for group, time, and their interaction, as well as a random intercept for students to account for within-subject correlations. A moderate treatment effect (*d* = .50) was applied at the post-intervention time point, and a smaller sustained effect (*d* = .20) was applied at follow-up. Simulated data included realistic between- and within-person variability, and the outcome variable was centered to aid model convergence. To reflect anticipated study conditions aligned with typical attrition in PA and mental health intervention research [76,77], the analysis included missing data at random in approximately 20% of observations, with a slightly higher dropout rate (30%) at the follow-up time point. All available data from each student will be used, aligning with an intention-to-treat analysis, and no ad hoc imputation will be performed, as researchers have suggested that linear mixed models without such imputation are more powerful than ad hoc strategies [78].

Based on 1,000 simulations, a total sample size of 114 students (~38 per group) yielded an estimated power of 98.10% (95% CI: 97.05, 98.85) to detect the group-by-time interactions using a Type II F-test with Satterthwaite degrees of freedom at α = .05. This high level of power reflects the modeled effect structure and supports the adequacy of the proposed sample size.

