### Objectives and hypotheses

Using a type 1 hybrid effectiveness-implementation study design [22], this three-arm parallel randomized controlled trial (RCT) will evaluate the effects of 1:1 and group-based supervised PA, compared to a 10-week waitlist control, among post-secondary students across three timepoints: baseline (T1), post-intervention (T2; 6-weeks), and follow-up (T3; 1-month post-intervention). Primary outcomes will include the immediate changes (T1–T2) in mental health indices (i.e., anxiety, depression, psychological distress, and well-being). Secondary outcomes will include changes from baseline to follow-up (T1–T3) and maintenance effects from post-intervention to follow-up (T2–T3) in mental health indices, as well changes in social well-being indices (i.e., social connectedness, social support), and PA behavior. The aims of the study include: (1) examining group differences between 1:1 PA delivery, group-based PA delivery, and the 10-week waitlist control arm on the primary and secondary outcomes; and (2) grounded in process evaluation recommendations [24], to explore implementation outcomes (i.e.,., reach, adherence, acceptability, fidelity) that may be linked to variation in primary and secondary outcomes while offering insight for wider dissemination. Based on evidence supporting various PA modalities for improving mental health [25], both 1:1 and group-based PA are hypothesized to be more effective than the waitlist control on primary and secondary outcomes, with no expected differences between the PA conditions on primary outcomes. Drawing on the social identity approach to health [20], it is hypothesized that group-based delivery will result in greater improvements in secondary outcomes including social well-being outcomes and maintenance effects compared to 1:1 delivery. However, 1:1 delivery is expected to yield more favourable implementation outcomes, due to its potential for stronger individualized support [14,26]. The results will provide novel insight into the effectiveness of different PA program delivery styles on student mental health, social well-being, and PA behaviour, while also offering implementation considerations to support the sustainability and scale-up of PA interventions across post-secondary campuses.

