### Allocation and blinding

Simple randomization will be used to allocate eligible students to the intervention arms using Research Randomizer [www.randomizer.org; 34,35]. Each student will be individually randomized, with an equal chance of being assigned to any of the three groups (1:1 PA, group-based PA, or waitlist control). While simple randomization may lead to unequal group sizes, block randomization was deemed unsuitable due to the risk of generating groups not comparable on covariates [34]. Stratified randomization was not possible given the continuous nature of student enrollment [34]. To account for the potential group size imbalance, primary statistical analyses will use linear mixed effects modeling, which are robust to unequal sample sizes and unbalanced data [36].

To minimize selection bias, allocation concealment will be used by having an investigator who will generate and assign random group allocations only after students have completed enrollment and the baseline (T1) assessment. Random allocations will be generated in real-time and not stored in advance. Students will be partially blinded in that students will be unaware of the purpose of group allocation or study hypotheses but will know they were assigned to an intervention arm or the control arm. To prevent care provider bias, PA coaches from Sport and Recreation Services will also not be informed about the purpose of group allocation or the study hypotheses. Investigators will not be blinded due to their roles in program coordination and statistical analyses. Recruiting an external individual to manage randomization, program coordination, and analyses is not feasible given the scope of the study and availability of resources. Nonetheless, several steps will be taken to minimize bias. Allocation concealment will be maintained until after baseline assessment, and analyses will follow the pre-specified plan outlined in this protocol paper. Outcome measures include open-ended and standardized self-report items, completed by students through a secure online data capture platform [REDCap; 37] without direct investigator involvement. The study protocol is also pre-registered to support transparency and reduce the risk of selective reporting.

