### Statistical analyses

Prior to conducting the main analyses, descriptive statistics will be calculated for baseline demographic characteristics (e.g., gender, age, sexual orientation, ethnicity/race) and main study variables at each assessment point (T1, T2, and T3) across the trial arms. To assess baseline equivalence between trial arms, differences in demographic characteristics and main study variables at baseline will be examined using chi-square tests and one-way analysis of variance. Differences in dropout will also be examined based on demographic characteristics and baseline study variables using chi-square tests and independent samples t-tests. The absence of systematic differences in dropout would support the plausibility of the Missing At Random (MAR) assumption, which underlies the use of linear mixed effects modeling in handling missing data [36,78,79].

For the main analyses, linear mixed effects modeling will be used to examine intervention effects on the primary and secondary outcomes over time and model assumptions will be tested [36,79]. Model specifications are provided above for a priori sample size calculation purposes. Models will be estimated using restricted maximum likelihood with the *lme4* and *lmerTest* packages in R Version 2025.05.0 + 496. The intra-class correlation coefficient (ICC) will be reported to quantify the proportion of total variance in the outcome attributable to between-person differences, relative to within-person changes across timepoints. Significant interactions will be probed using within-group and between-group pairwise comparisons conducted with the *emmeans* package. *P* value and *95% CI* adjustments using Tukey method for comparing a family of 3 estimates will be used to adjust for multiple comparisons.

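### The main model gives each arm its own T1 mean although T1 precedes allocation; the estimator is valid but forgoes precision on all four primary outcomes

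*Protocol article*

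**What the plan says.** The protocol article states the model under Sample size: "The model included fixed effects for group, time, and their interaction, as well as a random intercept for students". Statistical analyses adopts it for the main analyses by cross-reference: "Model specifications are provided above for a priori sample size calculation purposes". Neither section mentions a T1 covariate or a T1 mean shared by the arms.

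The primary target is a change: "Primary outcomes will include the immediate changes (T1–T2) in mental health indices" (Objectives and hypotheses). Comparisons between arms come afterwards: "Significant interactions will be probed using within-group and between-group pairwise comparisons" (Statistical analyses), using emmeans with a Tukey adjustment for three estimates. The section does not say whether the arms are compared on T2 means or on T1–T2 changes.

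Baseline is handled separately, by testing: "To assess baseline equivalence between trial arms, differences in demographic characteristics and main study variables at baseline will be examined using chi-square tests", together with one-way analysis of variance. No consequence for the model is attached to these tests. Allocation and blinding states that allocations are generated only once a student has enrolled and completed T1.

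**The concern.** With group, time and group-by-time terms all free, the model estimates nine separate means, three of them at T1. The T1–T2 interaction contrast is then in essence a difference between arms in change scores. Because T1 is measured before allocation, the three T1 means estimate the same quantity, and any observed difference between them is chance. A model that knows this can pool the T1 data over arms and weight T1 by its correlation with T2. The planned model subtracts T1 at full weight, so it carries noise that could be removed.

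At stake is the precision of the arm comparisons on depression, anxiety, distress and well-being, with about 38 students per arm and a substantial share of T2 and T3 values expected to be missing. A second matter is ambiguity. Under free T1 means, the T2 comparison and the T1–T2 comparison are different estimators with different standard errors, and the protocol does not settle which one the emmeans step will report.

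**Working it through.** **Inputs from the protocol article (Sample size).** 114 students, about 38 per arm; about 20% of observations missing and 30% at follow-up; "A moderate treatment effect (*d* = .50) was applied at the post-intervention time point" and "a smaller sustained effect (*d* = .20) was applied at follow-up"; α = .05; stated power 98.10% for the group-by-time F-test.

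**Assumptions.** The ICC (ρ) is not given, so a range is shown. T1 is taken as complete, since it precedes allocation, with 20% missing at T2 and 30% at T3. Outcomes are scaled to total SD 1, with the equal correlations that a random intercept implies.

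**The plan's own figure.** The 98.10% cannot be reproduced without ρ. With d on the total-SD scale and the missingness above, the 4-df interaction test has power 41.5%, 50.7% and 64.3% at ρ = .5, .6 and .7. It reaches 98.1% at ρ of about .89 (about .86 with complete data, about .90 if T1 is also 20% missing).

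**Complete-data formulas, two arms of n each.**
- Free T1 means, T1–T2 contrast: 4(1 − ρ)/n
- Common T1 mean or T1 covariate: 2(1 − ρ²)/n
- Free T1 means, T2 comparison: 2/n

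The second over the first is (1 + ρ)/2, a reduction of (1 − ρ)/2: 25%, 20% and 15% at ρ = .5, .6 and .7. The second over the third is 1 − ρ², a reduction of ρ². At n = 38 and ρ = .5, 4 × .5/38 = .0526 against 2 × .75/38 = .0395, and 1 − .0395/.0526 = 25%.

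**With the assumed missingness** (information matrix of the three-arm, three-visit model, with and without a common T1 mean):

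| ICC | SE of T1–T2 contrast, free T1 | SE, common T1 | Variance cut, T1–T2 contrast | Variance cut against T2-mean comparison |
|---|---|---|---|---|
| .3 | – | – | 30% | – |
| .5 | .248 | .220 | 21% | 21% |
| .6 | .223 | .203 | 17% | 31% |
| .7 | .194 | .181 | 13% | 44% |
| .8 | – | – | 8% | 59% |
| .9 | – | – | 4% | 78% |

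Check at ICC .6: (.203/.223)² = .83, a cut of 17%. In sample-size terms, 38 per arm with a common T1 mean is worth 38/.83, about 46 per arm, under the planned model.

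**Power for one pairwise T1–T2 contrast at d = .5.** Unadjusted: 52 to 62%, 61 to 69% and 73 to 79% at ICC .5, .6 and .7. Tukey-adjusted: 36 to 46%, 45 to 54% and 59 to 66%.

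**Sensitivity.** If T1 were also 20% missing, the variance cuts would be 29%, 24% and 19% at ICC .5, .6 and .7. At the ICC that the stated power would need (.86 to .90, according to the missingness assumed), the cut in the T1–T2 contrast is only about 5 to 7%, and just under 5% at .89 with T1 complete.

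**The case against.** The strongest reply is that the planned model is conventional, unbiased under randomization and matched to a change estimand, so that a common T1 mean is a refinement. At the ICC of about .89 implied by the stated power, the T1–T2 gain is negligible: Tukey-adjusted power moves from 97.1% to 97.7%. This stands in part. It is a matter of efficiency, and the gain may be small. But the ICC is unknown, the improvement is free, and a high ICC does not help if arms are compared on T2 means, where the loss grows with ICC.

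A reader might also infer stronger faults that the documents do not support:

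- **That baseline information is thrown away or the result biased.** T1 is a response in the model and is subtracted in the T1–T2 contrast. Only the equality of T1 means goes unused.
- **That chance T1 imbalance passes straight into the primary result.** The change contrast subtracts it; what remains is over-correction of about (1 − ρ) times the imbalance. Simple randomization is not to blame either: the remark "While simple randomization may lead to unequal group sizes, block randomization was deemed unsuitable" concerns group sizes, and unstratified blocking would leave the same chance differences in T1 scores.
- **That the random intercept inflates type I error.** No correlations are given, and the direction depends on their pattern. If correlation decays with time over the 6-week and roughly 4-week gaps, the T1–T2 standard error is overstated by about 2–3%, which is conservative. The protocol also says that model assumptions will be tested.
- **That the baseline tests cause the loss.** They say nothing useful under randomization, but they do not enter the model.

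**Conclusion.** The point holds as a loss of efficiency. The stated model leaves T1 means free by arm when the design makes them equal. On the T1–T2 contrast the avoidable variance is 30% at ICC .3, 21% at .5, 17% at .6, 13% at .7, 8% at .8 and 4% at .9, given 38 per arm, complete T1 and 20% and 30% missing at T2 and T3. None of these ICC values comes from the protocol, so no single figure should be quoted as the loss. If the emmeans step compares T2 means, the avoidable variance is about 21%, 31% and 44% at ICC .5, .6 and .7, and more above that. The planned analysis remains valid, and the change is a worthwhile improvement at almost no cost.

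**What to change.** State the main model as time plus arm-by-post-visit terms with one common T1 mean (no arm effect at T1). Alternatively, model T2 and T3 with T1 as a covariate. Either way, the T2 and T1–T2 between-arm contrasts become the same quantity, which settles what the emmeans step reports.

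Optionally, describe baseline by arm without significance tests, and refit with an unstructured covariance over the three visits as a sensitivity analysis.

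The cost is a few sentences and a few lines of R. No new data are needed, since T1 is already scheduled for every student. The article describes data collection as ongoing and already has a route for documented changes (Ethical considerations section). Because the investigators who analyse the data are not blinded, the choice should be recorded before outcomes are examined by arm.

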### Trial arms

Eligibility screening and randomization to trial arms will occur on a rolling basis, aligned with designated recruitment periods in the fall, spring, and summer semesters. All PA sessions will be delivered by trained Sport and Recreation PA coaches at the University of Toronto. Following group allocation to an intervention arm (1:1 or group-based PA), students will be matched with a coach and work with the same coach throughout the duration of the 6-week program. All PA sessions for the intervention arm are expected to commence within one week of randomization. Students assigned to 1:1 delivery will be matched immediately with a PA coach to coordinate weekly sessions. Group-based PA sessions will start once 3–8 students have been allocated and will be scheduled at a time that works for most students enrolled. Modifications to the allocated trial arm (e.g., switching from group to 1:1 PA delivery or from the control arm to an intervention arm) will not be permitted within the research protocol. However, students who are unable to follow through with their assigned trial arm will be offered PA sessions outside of the research (1:1 or group-based, depending on student preference) as part of standard service provision. Reasons for not initiating an assigned trial arm will be documented as part of the mixed methods process evaluation, as an indicator of adherence to the trial. To improve adherence to the intervention protocol by students, coaches will be in contact with students weekly to schedule sessions and will send reminder emails to students about upcoming sessions. To improve adherence to the intervention protocol by coaches, a standardized behavior change coaching booklet will be used to guide all PA intervention sessions. Regular bi-weekly check-ins with PA coaches and the research team will be conducted to support consistent delivery and to monitor implementation and student progression through the PA intervention. In addition, fidelity to core intervention processes will be examined based on student-reported experiences (see Implementation Process Evaluation Outcomes). Concomitant mental health care (e.g., therapy, medication use) and engagement in additional on-campus resources will be permitted during the trial and reported on to describe the student sample.

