### Group PA intervention delivery

The group PA intervention will receive the same protocol as described above though delivered in small groups of 3–8 students led by a trained Sport and Recreation PA coach. Drawing on group-dynamic principles [20,52], this number of students is ideal to help foster cohesiveness (e.g., through increased opportunity for interaction, discussion, and feedback/support from the PA coach) while reducing coordination and scheduling barriers. To promote needs satisfaction and preferences in group-based delivery, coaches will promote shared decision making on the types of activities engaged in within the group sessions.

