For the mixed methods process evaluation, quantitative closed-ended questions will be analyzed using descriptive statistics (means and standard deviations or frequency counts). Independent-samples t-tests and chi-square tests will be used to examine group differences between 1:1 and group delivery formats on process-related outcomes. Open-ended qualitative responses will be analyzed using thematic analysis [80]. An iterative coding process will be used, combining both an inductive (data-driven) and deductive (theory-informed) approach [81]. Findings from both quantitative and qualitative analyses will be integrated during interpretation in the discussion to provide a comprehensive understanding of student experiences and implementation processes.

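### The planned model and process tests ignore exercise groups of 3–8 students; if outcomes correlate within groups, group-arm standard errors are too small and the omnibus test exceeds its nominal 5%

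*Protocol article*

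**What the plan says.** Students are randomized one by one (Allocation and blinding: "Each student will be individually randomized, with an equal chance of being assigned to any of the three groups"). Clusters then form in one arm only. Group PA intervention delivery describes the programme as "delivered in small groups of 3–8 students led by a trained Sport and Recreation PA coach", and Trial arms states for both PA arms that "students will be matched with a coach and work with the same coach throughout the duration of the 6-week program". The Introduction and the group-delivery section expect cohesion, relatedness and peer interaction to act within these small groups. Intervention arms concedes that variation between coaches could plausibly cause bias.

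The model is given under Sample size: "The model included fixed effects for group, time, and their interaction", "as well as a random intercept for students to account for within-subject correlations". Statistical analyses takes this over for the main analyses by reference: "Model specifications are provided above for a priori sample size calculation purposes". The only ICC to be reported is the "proportion of total variance in the outcome attributable to between-person differences, relative to within-person changes across timepoints". For the process evaluation, "Independent-samples t-tests and chi-square tests will be used to examine group differences between 1:1 and group delivery formats on process-related outcomes".

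No section gives an exercise-group or coach effect, cluster-robust errors, a design effect, or a sensitivity analysis for clustering.

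**The concern.** Students who share sessions, peers and a coach may have outcomes that resemble each other more than those of students in different groups. The waitlist has no such structure, so the design is partially nested. The student intercept does not absorb a shared group effect. That effect arises after baseline, so it does not cancel from the change score and falls on the group-by-time contrast that the trial tests. Satterthwaite degrees of freedom do not help either, because they are computed for the random structure that the model contains.

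Two of the three between-arm comparisons involve the group arm. One is the comparison on which the protocol expects group delivery to outperform 1:1 delivery for social well-being. With too small a standard error, that expectation is confirmed by chance too often, and the intervals look more precise than they are. Process outcomes in which students rate a shared coach or shared sessions (COM-B fidelity, working alliance, enjoyment, acceptability) are open to the same problem.

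**Working it through.** **Inputs from the protocol.** About 38 students per arm (114 in total); groups of 3–8; d = .50 at T2 and .20 at T3; about 20% of observations missing and 30% at follow-up; omnibus interaction F-test at α = .05, then Tukey-adjusted pairwise comparisons of significant interactions.

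**Assumed, because the protocol gives no value.** Exercise-group ICC of 0.05 and 0.10 (0.10 and 0.20 for process ratings); within-person correlation of 0.5 to 0.88.

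**1. The plan's own figure.** 981 of 1,000 simulations gives an exact 95% interval of 97.05–98.85%, as printed. The 98.10% cannot be reproduced independently, because the variance components are not stated. With d in total-SD units, power was 0.415 at a within-person correlation of 0.5, 0.643 at 0.7 and 0.991 at 0.9. A simulation at 0.88 gave 0.978.

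**2. Number of groups.** 38/8 = 4.75 and 38/3 = 12.7, so about 5 to 13 exercise groups.

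**3. Group-arm design effect**, DE = 1 + (m − 1) × ICC, and effective n = 38/DE:

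| ICC | m = 3 | m = 5.5 | m = 8 |
|---|---|---|---|
| 0.05 | 1.10 (n 34.5) | 1.225 (n 31.0) | 1.35 (n 28.1) |
| 0.10 | 1.20 (n 31.7) | 1.45 (n 26.2) | 1.70 (n 22.4) |

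**4. Simulation of the planned random-intercept model.** No true effect, 38 per arm, 20% missing at T2 and 30% at T3, within-person correlation 0.7, a shared exercise-group effect at T2 and T3, 1,500 runs per cell. The contrast is group versus waitlist, T1–T2, unadjusted:

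| ICC, m | Omnibus error | Contrast error | Empirical / model SE |
|---|---|---|---|
| 0 | 4.7% | 4.5% | 0.191/0.193 = 0.99 |
| 0.05, 3 | 5.9% | 5.0% | 0.198/0.196 = 1.01 |
| 0.05, 5.5 | 6.6% | 7.6% | 0.210/0.195 = 1.08 |
| 0.05, 8 | 8.5% | 9.7% | 0.228/0.195 = 1.17 |
| 0.10, 3 | 5.9% | 8.7% | 0.222/0.198 = 1.12 |
| 0.10, 5.5 | 7.9% | 9.6% | 0.229/0.197 = 1.16 |
| 0.10, 8 | 10.1% | 11.5% | 0.242/0.197 = 1.23 |

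The Monte Carlo standard error near 5% is √(0.05 × 0.95/1500) = 0.6 percentage points, so single cells are noisy. At a within-person correlation of 0.5 the omnibus error was 4.4–6.1% (ICC 0.05) and 5.8–8.4% (ICC 0.10). A separate simulation at 0.7 gave 5.8–7.9% and 6.2–9.5%. Taken together, this is roughly 5–8% and 6–10%.

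**5. The procedure as planned** (omnibus gate, then Tukey for three comparisons; correlation 0.7, 1,500 runs per cell). The group-versus-waitlist T1–T2 contrast was falsely significant in 0.9% of runs without clustering, 1.5–2.7% at ICC 0.05 and 1.6–3.5% at ICC 0.10. Tukey without the gate gave 2.5–4.0% and 2.7–4.7%. A smaller check with 400 runs per cell put the gated rate at or below about 4%.

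**6. Rejection rate under the planned effects.** At correlation 0.88 and m = 5.5, with the group component set to 5–20% of the change variance, the omnibus test rejected in 96.5–97.7% of runs, against 97.8% without clustering.

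**7. Process t-tests, 1:1 versus group.** With equal arms and clustering in one, the SE is understated by √((1 + DE)/2).
- ICC 0.10: √(2.20/2) = 1.05 to √(2.70/2) = 1.16, so the true error is 6.2–9.2%.
- ICC 0.20 (DE 1.40 to 2.40): 1.10 to 1.30, so the true error is 7.4–13.3%.

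**The case against.** The strongest reply is that the size of the problem is assumed. The protocol gives no exercise-group ICC. Cohesion that helps every group equally moves the arm mean without making group-mates correlate; correlation needs groups to differ. That is right, and it makes the conclusion conditional. It does not justify fixing the correlation at zero when coaches, peers and sessions differ between groups.

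Second, the unadjusted contrast errors in step 4 (up to 11.5%) are not what the trial would report. A reader might infer that each published group-arm contrast carries an error of that order. The planned gate and Tukey adjustment do not support that: the per-contrast rate stays below 5%. What remains is inflation at the gate, a rise in the gated rate above 0.9%, and intervals that are too narrow, because Tukey widening does not correct the standard error beneath it.

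Third, a reader might infer that the trial is underpowered because of clustering. Step 6 does not support that. It describes the plan's own test, however, and power under a partially nested model was not computed.

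Fourth, not every process comparison is exposed. Delivery preference and initiation are largely individual responses, and the implementation outcomes are framed as exploratory. This stands.

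Finally, an article may leave detail to a full analysis plan. Here it names the random effect and the tests, and Allocation and blinding binds the analysis to the plan in this article as a safeguard for unblinded investigators. What is named assumes independence.

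**Conclusion.** The point holds conditionally. The stated model and process tests treat group-arm students as independent although delivery is clustered. If the within-group ICC is 0.05 to 0.10, group-arm standard errors and intervals are too small and the omnibus test runs at roughly 5–8% to 6–10% instead of 5%. The effect is slight for groups of 3 at an ICC of 0.05 and material for groups near 8 or an ICC of 0.10.

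Three limits apply:
- 1:1 versus waitlist is not affected by exercise-group clustering. Coach clustering could reach the 1:1 arm, but the number of students per coach is not stated.
- A group effect that is constant from T2 to T3 cancels from the T2–T3 comparison, so that comparison is affected only as far as the group effect changes.
- The flat statement that the standard errors are too small goes further than the documents allow, since it needs a positive ICC that they do not report.

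**What to change.** In Sample size and Statistical analyses, specify a partially nested mixed model. Keep the student intercept and add an exercise-group random effect that acts at T2 and T3 in the group arm only, with Satterthwaite or Kenward–Roger degrees of freedom. Report the exercise-group ICC beside the between-person one. For process outcomes that rate a shared coach or session, replace the independent-samples tests with the matching clustered model or small-sample cluster-robust tests. Add a coach random effect as a sensitivity analysis where coach and group can be separated; where a coach leads only one group they cannot.

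The cost is a change of analysis wording, best made before outcomes are examined, and group and coach identifiers carried into the analysis file. The protocol does not say that they are recorded there. Group-arm intervals will widen. With about 5 to 13 groups, the group variance will be imprecise and may be estimated as zero, in which case the fit reverts to the current model; the plan should say how that will be reported.
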